## Recruitment

Potential participants with MND and their caregivers will be identified and approached about the trial via local clinicians and clinical and research databases and via self-referral through community and online advertisements and talks to local MND Association support groups. Absence of a participating caregiver will not preclude a person with MND taking part in the trial. Once potential participants have been identified, consent for contact will be sought by the clinician (either verbally or with the use of a communication aid), where necessary. If consent is obtained, a member of the local research team will contact the potential participant to discuss the trial further and give them a participant information sheet.

If potential participants are interested in taking part in the study then they will be invited to attend a screening appointment with a member of the local research team (either in the clinic or home, by telephone, or by videoconference, depending on patient preference). Eligibility will be determined during the screening appointment. All eligible participants will be invited to provide fully informed written consent, verbal consent (for those who cannot provide written consent due to mobility difficulties or if verbal consent is being obtained by telephone or videoconference due to COVID-19 related restrictions), or consent via the use of a communication aid to participate in the trial, in line with Sheffield Clinical Trials Research Unit’s (CTRU) standard operating procedures (SOPs). An independent witness will be asked to sign the consent form to verify the consent taken in all cases where non-written consent is obtained in-person. In cases where verbal consent is obtained by telephone or videoconference, the conversation regarding consent will be audio recorded using an encrypted digital voice recorder, with the potential participant's agreement.

Therapists will be identified from the group of study therapists who will be involved in delivering the intervention to plwMND and approached by the trial’s research assistant. Other procedures will be similar to those described above.

### Randomisation

PlwMND will be allocated in equal proportions to one of two arms (ACT plus UC or UC alone) using a computer generated pseudo-random list. Randomisation will use blocks of varying length, stratified by recruitment site. The allocation sequence will be hosted by Sheffield CTRU in accordance with their SOPs and will be held on a secure server. Access to the concealed allocation sequence will be restricted to those with authorisation. A CTRU statistician will supply the allocation ratio (1:1) and block sizes to Sheffield CTRU’s bespoke online randomisation system (SCRAM). Eligible plwMND will be randomised once they have provided fully informed consent and baseline measures have been collected.

### Blinding

Trial statisticians will be blinded to allocation as per Sheffield CTRU SOPs. The outcome assessor will be intended to be blind to treatment allocation for the duration of the trial, while plwMND, carers, study therapists and clinicians will be aware of this. The Data Monitoring and Ethics Committee (DMEC) will have access to unblinded data at their request during the trial. Any instances of accidental unblinding will be recorded at 6 and 9 months, when the outcome assessors are asked to guess the allocated arm for each participant with MND.

### Data collection

Participants will be asked to provide fully informed consent prior to any data collection. Socio-demographic and clinical data will be collected at screening and baseline. Following confirmation of eligibility, the majority of outcome measures will be completed at baseline (0 months), 6 months post-randomisation (± 4 weeks), and 9 months post-randomisation (± 4 weeks). Exceptions to this are shown in Table 1. Data collection will be conducted via telephone, videoconference, post, email, online or via face-to-face interview by a blind outcome assessor. Mode of administration will be recorded as this may impact on the collection of some outcome measures. A range of strategies will be used to promote participant retention, including provision of flexible means to participate, newsletters and non-contingent vouchers for completion of follow-up outcome measures.

**Table 1 Tab1:**
[figure not shown]
Schedule of enrolment, interventions and assessments

*ACT*
Acceptance and Commitment Therapy, *ALS* amyotrophic lateral sclerosis, *p-r* post-randomisation, *UC* usual multidisciplinary care

a In order to avoid unblinding of outcome assessors, a question about the use of psychological therapies on the modified CSRI will be administered via post at 6 months and via the blinded outcome assessor at 9 months, after they have completed the unblinding question

b Completed after consent, but prior to randomisation, after participants are given a rationale for ACT

c Completed by the therapist at the end of their involvement in the trial

### Data management

Sheffield CTRU will oversee data collection, management and analysis and ensure the trial is undertaken according to Good Clinical Practice Guidelines and CTRU SOPs. Data will be collected and retained in accordance with The General Data Protection Regulation 2016/679. Participants will be assigned unique identification numbers and case report forms will not bear personal identifiable information apart from date of birth. Confidentiality will be maintained unless there is evidence of risk of harm to self or others. Data will be entered on a study database hosted on CTRU’s web-based data management system, Prospect. Prospect stores all data in a PostgreSQL database on virtual servers hosted by Corporate Information and Computing Services (CiCS) at the University of Sheffield. Prospect uses industry standard techniques to provide security, including password authentication and encryption using SSL/TLS. Encrypted audio files of verbal consents and therapy sessions will be recorded using encrypted digital voice recorders and uploaded to a secure server within University College London’s Data Safe Haven, which satisfies the highest level of security requirements of NHS trusts. All source documents will be securely retained for a period of 10 years following completion of the study.

### Quantitative analysis

A statistical analysis plan that includes the health economic analysis will be developed a priori and reviewed and approved by the Trial Steering Committee (TSC). The primary outcome measure will be analysed using a multi-level mixed effects model in which treatment group and baseline score will be included as fixed effect covariates and therapist will be included as a random effect to account for potential clustering. Analyses will be conducted separately at 6 months (the primary analysis time point) and 9 months. The difference between groups in mean quality of life will be quantified by the model coefficient, along with its 95% confidence interval. Primary analyses will be by intention to treat, but additional sensitivity analyses will be used to assess whether outcomes vary across sites/therapists, and by disease severity at baseline, psychotropic medication use, number of weeks taken to complete the therapy sessions and participants’ engagement in the intervention (as determined by the number of sessions completed within 4 months, and if applicable, whether the sessions were ongoing beyond 6 months post-randomisation).

Secondary outcome measures (for patients and caregivers) will be analysed in a similar fashion to the primary outcome measure. Adverse events will be summarised as the number and percentage of patients experiencing each event and the number of events by treatment arm. Patient deaths are expected to be relatively uncommon at 9 months (< 10%) and will be summarised descriptively as an adverse event. It is expected that some participants will have missing outcome data either due to death, loss to follow up or withdrawal from trial. The number of missing values will be summarised by treatment group, time point and reason. Multiple imputation using Rubin's rules [64] will be implemented for the primary and other key endpoints if the level of missing data exceeds 5% for reasons other than participant death.

Additional exploratory analysis will also be undertaken to assess the consistency of treatment effect across the following subgroups: i) severity of depression and/or anxiety at baseline, according to MND-specific clinical cut-offs on the Hospital Anxiety and Depression Scale [51]; ii) patient preference for treatment; iii) use of pharmacological therapy for mood disorder; and iv) disease severity as measured using the ALS Functional Rating Scale-Revised. We will also undertake exploratory analyses in those who score below clinical cut-offs for anxiety or depression at baseline on the Hospital Anxiety and Depression Scale to see whether ACT is beneficial in preventing progression to clinical levels of these symptoms at follow-up. In addition, we will conduct subgroup analyses to examine the potential impact of the COVID-19 pandemic on the reliability of trial results (with cut points for before and after the beginning of national lockdown on 23 March 2020 and before and after the final easing of lockdown restrictions on 27 January 2022).

The impact of non-adherence (i.e. non-uptake of ACT in the intervention group) and contamination (i.e. delivery of psychological therapy in the control group) will be assessed using complier-average causal effect analysis and a per-protocol analysis. Average Causal Response analysis will be used to assess any incremental impacts of the number of ACT sessions received [65].

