### Sample size

One hundred eighty-eight plwMND will be recruited from approximately 14 sites. This will allow detection of an effect size of 0.44 standard deviations, with a two-sided alpha of 5% and 90% power. This assumes 20% attrition at 6 months post-randomisation [59], an intra-class correlation coefficient of 0.01 among therapists (as used in other psychotherapy trials [60]) in the intervention arm, assuming 1 therapist per site and a correlation of 0.58 between 0 and 6 months post-randomisation for the McGill Quality of Life questionnaire in plwMND [59]. Our sample size is based on a clinically-meaningful pooled effect size of 0.44 standard deviations reported in a meta-analysis of ACT for mental and physical health conditions vs. controls [61], which falls within the range found for quality of life in studies of ACT in long-term conditions [62]. There are no published data with respect to what a clinically important difference is on the McGill Quality of Life Questionnaire-R in plwMND. However, our effect size is consistent with the minimal clinically important difference of 0.5 standard deviations that has been consistently reported for quality of life across different clinical populations [63].

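### The primary model leaves out recruitment site, the only stratification factor, so its confidence interval is somewhat too wide if sites differ

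*Protocol article*

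**What the plan says.** Protocol article, Randomisation: "Randomisation will use blocks of varying length, stratified by recruitment site". Allocation is 1:1, and no other stratification factor is named.

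Protocol article, Quantitative analysis: the primary outcome is analysed with a multi-level mixed model in which "treatment group and baseline score will be included as fixed effect covariates and therapist will be included as a random effect". Site is not a model term. It enters only through sensitivity analyses of whether outcomes vary between sites or therapists. Secondary outcomes for patients and caregivers are to follow much the same approach.

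Protocol article, Sample size: the calculation uses "an intra-class correlation coefficient of 0.01 among therapists", locates that clustering in the intervention arm, and does so "assuming 1 therapist per site". It contains no between-site variance.

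The article does not say how control participants, who have no study therapist, are coded for the therapist effect.

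**The concern.** Blocking within site balances site differences between the arms, so they largely cancel from the treatment contrast. An analysis gets the benefit only if the model knows about site.

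With one therapist per site and a therapist term confined to the ACT arm, the model cannot tell site variance from therapist variance in that arm. It treats both as clustering that makes the ACT mean less certain, and it treats controls at the same site as independent of one another and of the ACT participants there. The reported standard error then exceeds the true sampling variability. What is at stake is precision: an interval wider than it need be and a test that rejects too rarely.

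**Working it through.** **Inputs (Protocol article, Sample size).** "One hundred eighty-eight plwMND will be recruited from approximately 14 sites"; effect 0.44 SD; "with a two-sided alpha of 5% and 90% power"; 20% attrition; baseline to 6-month correlation 0.58; therapist ICC t = 0.01 in the ACT arm; one therapist per site.

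**Step 1: reproduce the stated size.**
- Residual variance after baseline adjustment: 1 − 0.58² = 0.6636.
- Per arm before clustering: 2 × (1.960 + 1.282)² × 0.6636 / 0.44² = 72.03.
- Analysed per arm: 188 × 0.80 / 2 = 75.2. Per therapist: m = 75.2 / 14 = 5.37.
- Design effect: 1 + (5.37 − 1) × 0.01 = 1.044.
- 72.03 × 1.044 = 75.2; 75.2 / 0.80 = 94 per arm; total 188.

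This applies the design effect to both arms. Applying it to the ACT arm only gives 184 to 188, depending on cluster size and rounding. The stated figure reproduces.

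**Step 2: true and reported standard error.** Let s be the site ICC as a share of residual variance (assumed, not in the article), and n = 75.2 per arm. With equal allocation within sites:
- True variance of the difference: (0.6636 / n) × [2(1 − s) + (m − 1)t]. The site effect cancels.
- Variance reported with an ACT-only therapist term and no site term: (0.6636 / n) × [2 + (m − 1)(s + t)].

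Example at s = 0.05:
- True: 0.008824 × (1.90 + 0.0437) = 0.01715, SE 0.1310.
- Reported: 0.008824 × (2 + 4.37 × 0.06) = 0.01996, SE 0.1413.
- Ratio: 1.079.
- Type I error: 2 × [1 − Φ(1.96 × 1.079)] = 3.45%.
- Power without site: Φ[(0.44 − 1.96 × 0.1413) / 0.1310] = 89.3%.
- Power with site: Φ[0.44 / 0.1310 − 1.96] = 91.9%.

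| Assumed s | True SE | Reported SE | Excess | Type I | Power, no site | Power, random site |
|---|---|---|---|---|---|---|
| 0 | 0.1343 | 0.1343 | 0% | 5.0% | 90.6% | 90.6% |
| 0.01 | 0.1336 | 0.1357 | 1.6% | 4.65% | 90.4% | 90.9% |
| 0.02 | 0.1330 | 0.1371 | 3.1% | 4.3% | 90.1% | 91.1% |
| 0.05 | 0.1310 | 0.1413 | 7.9% | 3.45% | 89.3% | 91.9% |
| 0.10 | 0.1276 | 0.1480 | 16% | 2.3% | 88.0% | 93.2% |

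**Step 3: simulation check.** REML fits, 1,500 trials per setting, 150 analysed, 14 unequal sites. The Monte Carlo standard error on power is √(0.9 × 0.1 / 1500), about 0.8 points.

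| Assumed s | Mean reported SE v empirical SD (null) | Type I, no site | Power, no site | Power, random site | Power, fixed site |
|---|---|---|---|---|---|
| 0 | 0.138 v 0.136 | 4.9% | 90.6% | 90.9% | 87.9% |
| 0.01 | 0.139 v 0.136 | 4.9% | 87.9% | 88.8% | 86.8% |
| 0.05 | 0.143 v 0.133 | 4.2% | 89.1% | 90.7% | 90.1% |
| 0.10 | 0.148 v 0.128 | 2.3% | 87.3% | 91.6% | 90.6% |

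The models were fitted to the same simulated data, so differences within a row are more reliable than differences between rows. Direction and rough size agree with the closed form. With a random site effect, type I error was 4.9% to 5.5%.

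**Step 4: how far baseline adjustment helps.** If site differences are already present at baseline and persist unchanged (an assumption), about (1 − 0.58)² = 18% of the site variance remains after adjustment. Site variance of 5% or 10% of total variance then becomes s of about 0.05 × 0.176 / 0.6636 = 0.013, or 0.027. The standard error is about 2% or 4% too large, and power stays near 90%. If none of a 5% share of total variance were explained by baseline, s would be 0.05 / 0.6636 = 0.075 and the excess about 12%.

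**The case against.** The strongest reply is that the fault is conditional and benign. The article gives no between-site variance. At zero there is no loss, and at 0.01, the value assumed for therapists, the excess is under 2% and the power loss about half a point to one point. The estimate is unbiased, the test is conservative, and site is examined in sensitivity analyses. All of this stands and limits the weight of the point.

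The ACT-only form of the therapist term is also inferred. With one therapist per site, linking controls to their site's therapist would make the term act much like a site effect, and most of the problem would go. The announced analysis plan or the full protocol, neither shown, may settle this. That also stands. It does not remove the point, because the article names the terms of its primary model and the stratification factor is not among them.

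A reader might go further in two ways. One is to infer that the trial misses its 90% power even if every sample size assumption holds. It does not: those assumptions include no site variance, and under them power is about 90% with or without site. The other is to suppose that all controls share a single no-therapist cluster in a plain random intercept, which would cost far more power. Nothing in the article says so, and the Sample size section points away from it by placing therapist clustering in the intervention arm.

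**Conclusion.** The point holds in a limited form. The stated primary model omits the only stratification factor, and under an ACT-only therapist term this makes the confidence interval too wide when sites differ. Over an assumed residual site ICC of 0 to 0.10, the excess in the standard error runs from 0% to about 16%, type I error falls from 5.0% to about 2.3%, and power without site is about 91% down to 88%, against 91% up to 93% with a random site effect. The loss is smaller to the extent that baseline score already carries the site differences. There is no bias and no inflation of false positives, and the sample size of 188 needs no revision. This is an inexpensive gain in precision, not a threat to the trial's validity.

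**What to change.** In the primary model, add recruitment site as a random intercept in both arms, and specify therapist as a random effect in the ACT arm only (a partially nested model), stating that controls carry no therapist level. Controls at each site let the model separate site from therapist variance even with one therapist per site. Use the same model for the secondary outcomes that follow the primary analysis.

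The cost is a sentence in the analysis section or the analysis plan and one extra variance parameter, with no new data. If fixed site effects are kept as a fallback for non-convergence, note that they can cost up to about 3 points of power when site variance is near zero (87.9% against 90.6% without site in the simulation), although they gain power once the site ICC reaches about 0.05.

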It has been argued that ACT may be particularly suited to improving outcomes in objectively difficult or immutable situations, such as life-limiting illnesses and chronic conditions [20–24]. As there is no cure for MND, helping people to live their life as best they can alongside MND is likely to be a more pragmatic approach than trying to control or get rid of distressing or difficult experiences. Furthermore, there is evidence that ACT processes such as psychological flexibility predict functioning and quality of life in MND [25] and other progressive, incurable and/or life-limiting conditions, including muscle disorders [26–28], Duchenne muscular dystrophy [29] and palliative care populations [30]. Finally, there is emerging preliminary evidence that ACT might have advantages over conventional CBT through improved engagement, retention and durability of effects [31–34].

To our knowledge, there have been no trials of ACT for plwMND to date. We showed that ACT was feasible to deliver and acceptable to plwMND in an open uncontrolled feasibility study [35]. We will now assess the clinical and cost effectiveness of ACT, modified for plwMND, plus usual multidisciplinary care (UC) in comparison to UC alone for improving psychological health in plwMND.

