Secondary outcome measures will be as follows:Hospital Anxiety and Depression Scale [50]: A 14-item self-report measure of depression and anxiety, which provides separate scores for depression and anxiety, as well as an overall score. For the purpose of analysis and, following validation in plwMND and subsequent published recommendations [51], a subset of data will be analysed which omits one item on the depression scale that assesses psychomotor retardation and one item on the anxiety scale that assesses restlessness as these overlap with physical symptoms of MND;Acceptance and Action Questionnaire-II [52]: A 7-item self-report measure of psychological flexibility (an ACT-specific coping measure);EQ-5D-5L [53]: A 5-item self-report measure of health-related quality of life, used to calculate utility scores for use in economic evaluations. Each of the 5 items is rated on a 5-point scale from no problems to extreme problems. This will be collected from both plwMND and caregivers;Non-physical adverse events and physical self-harm;ALS Functional Rating Scale-Revised [54]: The self-administered version of a 12-item measure of function that has been developed for plwMND will be used as an indicator of disease progression;Existential and Psychological subscales of the McGill Quality of Life Questionnaire-R [45]^,2^: These subscales have been included as secondary outcome measures as quality of life in MND (and hence psychological health) has been found to be more associated with psychological/existential factors than physical function/strength [49];Survival at 9 months;Satisfaction with Therapy and Therapist Scale-Revised [55]: A 12-item self-report measure of satisfaction with therapy and satisfaction with the therapist, rated on a 5-point scale from 1 (strongly disagree) to 5 (strongly agree). Six items relate to satisfaction with therapy and six to satisfaction with the therapist;Client Service Receipt Inventory (CSRI) [42] modified for plwMND. This information will be extracted from participants' self-reports, GP medical records and/or MND care centre records, with participants' consent;Quality-adjusted life years and resource use to inform the cost-effectiveness analysis;Zarit Burden Interview [56]: A well-validated 22-item self-report measure of caregiver burden, which will only be collected from caregivers.

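### Optional improvement: the primary model is valid with baseline score alone, but adding baseline ALSFRS-R and modified HADS would buy modest precision and guard against arm-differential dropout

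*Protocol article*

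**What the plan says.** The protocol article's Quantitative analysis section fixes the primary model: "treatment group and baseline score will be included as fixed effect covariates and therapist will be included as a random effect". The 6-month and 9-month outcomes are modelled separately, and 6 months is primary.

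Two other measures matter here. On the ALSFRS-R the Outcomes section reads "developed for plwMND will be used as an indicator of disease progression". The same section lists the HADS, analysed with two items removed because they overlap with physical symptoms of MND. Data collection says most measures are taken at baseline, and Randomisation says baseline measures come before allocation. Quantitative analysis uses baseline disease severity in a sensitivity analysis, and baseline HADS severity and ALSFRS-R in exploratory subgroups. Neither enters the primary model.

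On missing outcomes, the section states: "It is expected that some participants will have missing outcome data either due to death, loss to follow up or withdrawal from trial". It then plans multiple imputation for the primary endpoint if more than 5% is missing for reasons other than death.

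The Sample size section sets the total at 188 across about 14 centres and makes this claim for it: "This will allow detection of an effect size of 0.44 standard deviations, with a two-sided alpha of 5% and 90% power". Loss by 6 months is put at one in five. For clustering in the ACT arm the section takes "an intra-class correlation coefficient of 0.01 among therapists", with a single therapist at each site. The baseline and 6-month scores are taken to correlate at 0.58.

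**The concern.** The covariate set is stated in the protocol, not deferred, and it omits two baseline variables that the protocol itself treats as relevant to progression and distress. Two things are at stake.

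The first is precision. A prognostic baseline covariate lowers the residual variance in a linear model without changing the treatment contrast being estimated, so leaving it out gives up some power.

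The second is bias from loss to follow-up. One in five participants is expected to have no 6-month score. Participants know their arm, only one arm is offered up to eight therapy sessions, and the control is usual care. If the rate of loss, or its dependence on severity or distress, differed between arms, the participants remaining in the two arms would differ in prognosis in ways that baseline MQOL-R captures only in part.

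**Working it through.** **Inputs from the Sample size section.** Effect 0.44 SD, two-sided 5%, power 90%, attrition 20%, ICC 0.01, r = 0.58, about 14 sites with one therapist each, total 188.

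**Inputs not in the document (assumptions).** The partial R² of the added covariates given baseline MQOL-R, and how dropout depends on severity.

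**Step 1: the plan's own figure.** With ANCOVA on baseline score, the residual variance is 1 − 0.58² = 0.6636.

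- n per arm = 2 × 0.6636 × (1.960 + 1.282)² / 0.44² = 72.03
- Design effect = 1 + (75/14 − 1) × 0.01 = 1.044, giving 75.17 analysed per arm
- Inflate for attrition: 75.17 / 0.8 = 93.96, so 94 per arm and **188 in total**

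The stated figure reproduces exactly. Applying the design effect to the intervention arm only gives 186. The model and the sample size therefore agree, and the 90% power does not depend on further covariates.

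**Step 2: precision gain.** Analysed per arm: 188 × 0.8 / 2 = 75.2. With the design effect in the ACT arm only,

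SE = √[0.6636 × (1 − R²) × (1 + 1.044) / 75.2], and power = Φ(0.44/SE − 1.96).

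| Assumed partial R² | SE | 95% CI half-width (SD) | Power | N for 90% power (Step 1 formula) |
|---|---|---|---|---|
| 0 (as planned) | 0.1343 | 0.263 | 90.6% | 188 |
| 0.02 | 0.1329 | 0.261 | 91.1% | 186 |
| 0.05 | 0.1309 | 0.257 | 92.0% | 180 |
| 0.10 | 0.1274 | 0.250 | 93.2% | 170 |

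The interval shrinks by the factor √(1 − R²), which is 0.990, 0.975 and 0.949: about 1%, 2.5% and 5%. A noncentral-t version gives 90.2% as planned and 90.8%, 91.6% and 92.9% with the covariates.

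**Step 3: bias from dropout.** Large-sample simulation (2,000,000 participants): true effect 0.44 SD, r = 0.58, one severity covariate correlated 0.3 with baseline score, dropout logistic in that covariate (slope 0.8 per SD unless noted). The entries are the error of the baseline-score-only estimate, in SD.

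| Dropout scenario | Missing, control v ACT | R² 0.05 | R² 0.10 | R² 0.20 |
|---|---|---|---|---|
| Same in both arms | 19% v 19–20% | +0.003 | +0.002 | 0.000 |
| Same slope, different rates | 27% v 11% | −0.021 | −0.027 | −0.038 |
| Slope twice as steep in control | 19% v 19% | −0.011 | −0.017 | −0.023 |
| Severity-related in control only | 19% v 19% | −0.026 | −0.036 | −0.051 |

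With the covariate in the model, every scenario is within 0.003 of zero. The sign depends on which arm carries the stronger link. A separate simulation at N = 188, with slopes 1.2 and 0.3 in the two arms and partial R² 0.022, 0.048 and 0.102, gave 0.458, 0.469 and 0.484 one way and 0.417, 0.412 and 0.398 with the arms reversed. The adjusted model gave 0.437–0.442.

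**Step 4: is the imputation trigger met?** Attrition is 20% at 6 months and deaths are expected to be under 10% even at 9 months. Non-death missingness is then above 20% − 10% = 10%, which exceeds 5%. On the protocol's own figures, imputation would be done.

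**The case against.** The strongest reply is that nothing is wrong. ANCOVA on the baseline score with a therapist random effect is a sound pre-specified analysis and delivers the stated power. That stands in full.

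A reader might infer that dropout related to severity biases the primary estimate by itself. The documents do not support this: Step 3 shows essentially no bias when such dropout is alike in both arms, and nothing in the protocol predicts a difference between arms. It remains possible because participants are not blinded.

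A reader might also infer that the plan rests on available cases only. It does not, because multiple imputation is planned and its trigger should be met. With ALSFRS-R and HADS as auxiliary variables, imputation would largely deal with the same bias. Listing those variables is normally left to the SAP, so their absence here is no fault. Imputing from arm and baseline score alone, however, would leave that bias in place. Even with the auxiliaries, imputation does not give the full precision gain of adjustment. The planned severity sensitivity analyses do not change the primary estimate.

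The support for the covariates' strength is also limited. The Background says "there is evidence that ACT processes such as psychological flexibility predict functioning and quality of life in MND", but that concerns a construct measured by a different questionnaire. The Outcomes section says physical function is less closely related to quality of life than psychological and existential factors, which weakens the case for ALSFRS-R. HADS overlaps with the Psychological domain already inside baseline MQOL-R. The partial R² may therefore sit at the low end of the range.

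**Conclusion.** A free improvement of optional severity, not an error or a contradiction. For an assumed partial R² of 0.02 to 0.10, which the document does not give, power rises from about 90% to 91–93% and the interval narrows by about 1–5%.

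The bias protection is small and conditional: about 0.01 to 0.05 SD, in either direction, only if dropout or its link to severity differs between arms. That compares with a target of 0.44 SD and a confidence-interval half-width of about 0.26 SD. The near-perfect correction in the simulations reflects their assumption that dropout depends on the covariate being added. Dropout that depends on the unseen 6-month outcome would not be corrected by any baseline covariate. It would be wrong to conclude that the trial is underpowered or that its primary estimate is biased as planned.

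Table 1 is not shown, so baseline collection of both measures is taken from the Data collection text and from their use as baseline severity variables in the planned analyses.

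**What to change.** Before unblinding, in the SAP and with the change from the published protocol recorded:

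- Add baseline ALSFRS-R total and baseline modified-HADS total, both continuous and linear, as fixed effects in the primary 6-month model.
- Use the same two variables in the multiple imputation already planned.
- Keep the model with treatment group, baseline score and therapist as a sensitivity analysis.
- In patient secondary-outcome models, do not enter a measure alongside its own baseline score or an overlapping total. The ALSFRS-R model would gain only HADS. The HADS models, including the subscales, would gain only ALSFRS-R.
- Leave the caregiver models unchanged.

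The cost is wording and two degrees of freedom among about 150 analysed (188 × 0.8 = 150.4). No new data are needed. A short rule for an occasional missing baseline covariate should be added, so that no participant leaves the primary model for that reason.
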